# 8 Design

The *TeachMeToBuild* trial is designed as a pragmatic, open-label, 2x2 factorial, cluster randomized, controlled, superiority study. Each cohort (cluster) will be randomized in a 1:1 allocation ratio to the self-report tool for distress using a stratified, permuted-block group schema according to the following strata:

1) Study site (Sudbury, Barrie)

The MH&A fit-for-purpose service will only be available to apprentices located at the Barrie site.

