**Figure 1: 2x2 factorial design for case management strategies**

|  | Self-report tool for distress | |
| --- | --- | --- |
| MH&A Service | Control | Intervention |
| Control (Sudbury) | BCM | ICM^10^ |
| Intervention (Barrie) | ICM^01^ | ICM^11^ |

In this 2x2 factorial design, the intervention effects for 3 ICM models will be estimated. For the cohorts located in Sudbury, the current standard of case management will be the BCM model. The reason for this is the absence of a working relationship between Community Builders® and the MH&A program at Health Sciences North, the healthcare authority for the greater Sudbury region, that would permit the establishment of a similar fit for purpose service as the one created for the Barrie cohort. In this BCM model, the Training Program Coordinator in Sudbury will host bi-weekly meetings with each apprentice to ensure that all boundaries to skilled trades employment are eliminated. This includes, but is not limited to, check-ins (frequency) with the apprentice through Slack, frequent visits to the construction sites, and monitoring of the feedback forms that mentors complete weekly on the attendance, attitude, and coachability of their apprentice. For the ICM^10^ and ICM^01^ models, this BCM model will serve as the control for estimating the effects of the self-report for distress tool and the MH&A program, respectively. For the ICM^11^ model, both the ICM^10^ and the ICM^01^ models will serve as the controls to estimate the interaction effect for the combined self-report for distress tool and the MH&A program.

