# 6 Hypotheses

## 6.1 Primary

In apprentices enrolled in the TDTP who are at-risk of absenteeism, drop-out or unemployment post-program completion, exposure to either the ICM^10^ or ICM^01^ models will be superior to the BCM model for reducing absenteeism (as determined by the number of absence-free days), drop-out (as determined by the proportion of apprentices completing the program), and unemployment (as determined by proportion employed at 24 months post-program completion).

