## 14.1 Difference in proportion of AFDs

The sample size is fixed at approximately 448 individuals. We anticipate that the first few cohorts will be asked to pilot the screening tool, potentially removing up to 50 apprentices from the final sample size. We will use a fixed sample size of 400 apprentices, divided equally between Sudbury and Barrie sites. The expected cohort sizes will range from 6 to 10 apprentices, resulting in 20 to 34 cohorts per site. We will use a 3-level hierarchical design to model differences in proportion of AFDs where the daily attendance (Level 1) will be coded as binary; 0 for absence and 1 for attendance. Level 1 observations are clustered within individual apprentices (Level 2), which are nested within individual cohorts (Level 3). The sites (Sudbury and Barrie) and start date of cohort enrollment (q1 (January-March); q2 (April-June); q3 (July-Sept); q4 (Oct-Dec) and year) will be included as confounding variables in Level 1 and will not enter into the power calculations. Using this design, we performed a sensitivity analysis to determine the power to observe different primary outcome effect sizes with an $\alpha$-level 0.05**.**  As can be seen in the following table, even small differences in attendance (5% difference in proportions of AFDs) would still be detected with power ≥ 80% as long as the Level 2 inter-cluster correlation ≤ 0.125, a very reasonable assumption as there is no reason to believe that these apprentices’ attendance behaviours will be highly correlated with each other (23).

|  | **Scenarios**^1^ | | | | | | | |
| --- | --- | --- | --- | --- | --- | --- | --- | --- |
| **Variables** | 1 | 2 | 3 | 4 | 5 | 6 | 7 | 8 |
| Test Significance Level, α​ | 0.05 | 0.05 | 0.05 | 0.05 | 0.05 | 0.05 | 0.05 | 0.05 |
| Mean Difference, δ = µ₁ - µ₂​ | 0.1 | 0.15 | 0.05 | 0.05 | 0.05 | 0.05 | 0.05 | 0.1 |
| Standard Deviation, σ​ | 0.1 | 0.1 | 0.1 | 0.1 | 0.1 | 0.1 | 0.15 | 0.15 |
| Level 1 Unit Correlation, ρ₁​ | 0.75 | 0.75 | 0.75 | 0.75 | 0.75 | 0.75 | 0.75 | 0.75 |
| Level 2 Unit Correlation, ρ₂​ | 0.5 | 0.5 | 0.5 | 0.25 | 0.125 | 0.05 | 0.05 | 0.05 |
| Number of Level 3 Units in Group 1, C₁​ | 15 | 15 | 15 | 15 | 15 | 15 | 15 | 15 |
| Number of Level 3 Units in Group 2, C₂​ | 15 | 15 | 15 | 15 | 15 | 15 | 15 | 15 |
| Level 3 Units per Group Ratio, C₂/C₁​ | 1 | 1 | 1 | 1 | 1 | 1 | 1 | 1 |
| Number of Level 2 Units per Level 3 Unit, K​ | 6 | 6 | 6 | 6 | 6 | 6 | 6 | 6 |

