# 16 Allocation

## 16.1 Sequence generation

Cohorts will be randomly assigned to either BCM or ICM^1x^ (Figure 1) with a 1:1:1:1 allocation schema as per a computer-generated randomisation schedule stratified by site using permuted blocks of size 4 in each strata. A single block size was chosen to accommodate potentially different cohort numbers resulting from variation in the cohort sample sizes. The block size will not be disclosed to ensure concealment.

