# 30 Post-trial care

Should this study provide evidence of the superior effectiveness of using the Distress Thermometer and/or MH&A care pathways compared to usual case management, subsequent TDTP or similar construction vocational programs administered by Community Builders Construction will incorporate similar case management strategies.

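### The MH&A service is assigned by site, not by randomisation, so ICM01 versus BCM and the MH&A effect cannot be separated from Barrie versus Sudbury

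*Protocol*

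**What the plan says.** - **What is randomised.** Section 8: "Each cohort (cluster) will be randomized in a 1:1 allocation ratio to the self-report tool for distress", stratified by site. The same section adds: "The MH&A fit-for-purpose service will only be available to apprentices located at the Barrie site".
- **Layout.** Figure 1 in Section 5.3 has the row "Control (Sudbury) | BCM | ICM^10"; the other row is Barrie, with ICM01 and ICM11. The text below the figure explains that the sponsor's partner has no working relationship with the Sudbury health authority. It then names BCM as the control for estimating the MH&A effect through ICM01.
- **Claims.** Section 6.1 states as the primary hypothesis that "exposure to either the ICM^10^ or ICM^01^ models will be superior to the BCM model". Section 7.1 repeats ICM01 versus BCM in primary objectives 1–3 and adds ICM11 versus ICM10 in objectives 4–6. The scientific title in Section 1.1 calls the whole study a cluster randomized 2x2 factorial. Section 30 ties later adoption to "evidence of the superior effectiveness of using the Distress Thermometer and/or MH&A care pathways compared to usual case management".
- **Allocation.** Section 16.1 assigns cohorts to BCM or ICM1x "with a 1:1:1:1 allocation schema as per a computer-generated randomisation schedule stratified by site using permuted blocks of size 4 in each strata".
- **Analysis.** Section 14.1 says that site and the start date of the cohort "will be included as confounding variables in Level 1 and will not enter into the power calculations". The models in Section 20.11 enter the tool, MH&A, their interaction, and time period with its interactions. They do not list site.

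**The concern.** A factorial trial gives randomised evidence on both factors only if both are allocated by chance. Here one factor follows geography. ICM01 versus BCM, ICM11 versus ICM10 and the MH&A main effect are all comparisons of Barrie cohorts with Sudbury cohorts. Differences in labour market, applicants, training staff, mentors or local health services would be credited to MH&A.

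The protocol's own description of the sites (Section 9) gives reason to expect differences. Unemployment is 6.0% in Barrie and 8.5% in Sudbury, Indigenous residents 2.1% and 17.5%, visible minorities 6.7% and 1.2%, and French-only speakers 1% and 24.7%. Full-time employment is a primary outcome, so the labour-market gap bears on it directly.

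With one site per level of MH&A there is no replication from which to estimate between-site variation. Standard errors clustered on cohort describe variation among cohorts within a site and leave the site difference out. The result would be a Barrie–Sudbury contrast presented as randomised superiority on a primary hypothesis, and used to support roll-out.

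**Working it through.** **1. The plan's own power figures.** Section 14.2, scenario 5: 200 per group, 0.90 versus 0.80, ICC 0, two-sided α 0.05. With pooled variance under the null:

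z = (0.10·√200 − 1.96·√(2·0.85·0.15)) / √(0.90·0.10 + 0.80·0.20) = (1.414 − 0.990)/0.500 = 0.849, so power is 80.2%. The protocol states 80.2%.

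Dividing n by the design effect 1 + (M−1)·ICC, scenario 2 (0.85 versus 0.75, ICC 0.05, M = 10, design effect 1.45) gives 54.7%, against 54.6% stated. All seven completion scenarios reproduce to within 0.1 point. The arithmetic is sound; the problem lies in what the comparison identifies.

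**2. Identifiability.** Take 20 cohorts per site, half with the tool, with site = 1 for Barrie and MH&A = 1 wherever the service exists.

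| Columns | Number | Rank |
|---|---|---|
| intercept, site, MH&A, tool, MH&A×tool | 5 | 4 |
| the same plus site×tool | 6 | 4 |

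The correlation of site with MH&A is 1. It follows that:
- the MH&A main effect, ICM01 versus BCM and ICM11 versus ICM10 equal the MH&A effect plus the site effect;
- MH&A×tool equals site×tool. A constant site effect cancels from the interaction on the model scale, but any difference between sites in how the tool works does not;
- ICM10 versus BCM (within Sudbury), ICM11 versus ICM01 (within Barrie) and the site-stratified tool effect are free of this confounding.

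**3. Size under an assumed site gap.** Set the true MH&A effect to zero and let site alone move completion from p0 to p1.

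- SE = √{[p0(1−p0) + p1(1−p1)]·[1 + (m−1)·ICC]/n}
- Rejection rate = Φ(d/SE − 1.96) + Φ(−d/SE − 1.96), with d = p1 − p0
- n = 200 per side for the MH&A main effect (400 split equally by site, Section 14.1) and about 100 per side for ICM01 versus BCM (tool 1:1 within site)
- p0 = 0.75, ICC = 0.05 (Section 14.2) and m = 6 to 10 (Section 14.1); the gaps d are assumptions.

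Example: d = 0.05, m = 10, n = 200. SE = √(0.3475·1.45/200) = 0.0502, d/SE = 0.996, rejection rate 16.8% + 0.2% = 16.9% after rounding.

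| Assumed gap | m | MH&A main effect (200 vs 200) | ICM01 vs BCM (100 vs 100) |
|---|---|---|---|
| 0.75 → 0.80 | 6 | 18.9% | 11.8% |
| 0.75 → 0.80 | 10 | 16.9% | 10.8% |
| 0.75 → 0.85 | 6 | 61.6% | 35.7% |
| 0.75 → 0.85 | 10 | 55.3% | 31.6% |

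The nominal rate is 5%. Over the wider range p0 = 0.75–0.80 and ICC 0–0.05, with 10 per cohort where ICC is above 0:

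| Assumed gap | MH&A main effect | ICM01 vs BCM |
|---|---|---|
| 2 points | 7–8% | 6–7% |
| 5 points | 17–26% | 11–15% |
| 10 points | 55–81% | 32–52% |

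Enlarging the sample at these two sites leaves the bias unchanged and shrinks the SE, so the false-positive rate rises.

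**4. Allocation text.** Read literally, 1:1:1:1 in blocks of 4 within each site would place ICM01 and ICM11 in Sudbury, and BCM and ICM10 in Barrie. Section 8 makes that impossible.

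**5. Site as a covariate.** Section 14.1 puts site into the same three-level attendance model that Section 20.11a specifies with MH&A. Both cannot be estimated. If one is dropped, the remaining coefficient carries both effects.

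**The case against.** The strongest reply is that the protocol hides nothing. It says that MH&A exists only in Barrie and why, and Section 30 is conditional and limited to one provider's programmes. That is true, but neither Section 5.3 nor Section 8 draws the consequence for inference, and Sections 6.1 and 7.1 treat the contrast as a primary superiority test.

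Several narrower points stand in part:
- **The tool factor is sound.** Half of the primary hypothesis, ICM10 versus BCM, is a randomised within-site comparison. The fault lies with the MH&A factor and with crediting the interaction to MH&A.
- **Section 16.1 can be read more kindly.** BCM or ICM1x may mean no tool or tool. With equal sites, 1:1 within each site gives four equal cells overall, and blocks of 4 suit that as well. The literal text still conflicts with Section 8.
- **No model in Section 20 lists both site and MH&A.** The clash is between Section 14.1 and Section 20.11. Leaving site out does not remove the confounding; it only makes it less visible.
- **The Section 9 figures describe cities, not enrollees.** Both sites recruit under the same programme criteria, and low-income prevalence is 11.6% in both. The figures show that the sites may differ, not by how much on the trial outcomes.
- **The inflation is smaller for ICM01 versus BCM** than for the main effect, because the cells are about half the size. Both are shown above.

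**Conclusion.** The concern holds. As written, the plan tests a non-randomised two-site comparison as a primary superiority hypothesis of a randomised factorial trial. The bias equals the site difference, and no covariate adjustment or analysis model can remove it, so a separate statistical analysis plan could not repair it.

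That conclusion follows from Sections 5.3 and 8 and needs no numerical assumption. The false-positive rates do: they rest on assumed completion gaps between sites of 2 to 10 points, a base rate of 0.75–0.80, ICC 0–0.05 and a normal approximation. At a 5-point gap with base rate 0.75 and ICC 0.05 they are about 17–19% for the MH&A main effect and 11–12% for ICM01 versus BCM. The randomised tool effect, within site or pooled with stratification by site, is unaffected. This must be corrected before the results are interpreted.

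**What to change.** 1. Describe the trial in the title and in Sections 1.1, 5.3 and 8 as a cluster randomised trial of the self-report tool, 1:1 within site.
2. In Sections 6 and 7, make the primary comparison tool (ICM10 + ICM11) versus no tool (BCM + ICM01), stratified by site. At about 200 versus 200 this is the comparison that Section 14.2 powers. ICM01 versus BCM, at about 100 per cell, has only about 31–51% power for a 0.10 difference.
3. Report ICM01 versus BCM, ICM11 versus ICM10 and the MH&A main effect as non-randomised site comparisons without a superiority claim. Describe the interaction as a difference in the tool effect between sites, not attributable to MH&A.
4. In Section 16.1, replace 1:1:1:1 by 1:1 tool versus no tool within each site.
5. Reconcile Section 14.1 with Section 20: use one indicator for site/MH&A, named as both.
6. Take MH&A out of the adoption statement in Section 30.

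Randomised evidence on MH&A would require chance allocation of access among cohorts within a site. Whether that is possible is for the sponsor to say.

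**Cost.** Objectives and design change, so Section 25 requires a formal amendment with Research Ethics Board approval, and the registry entry must be updated. No participants are added. What is lost is the randomised label on MH&A, which the design does not support.

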# 9 Study Setting

Community Builders® is a not-for-profit construction-based social enterprise (<https://www.communitybuilders.co/about-us/>) with offices in Simcoe County (Barrie) and Greater Sudbury. The enterprise offers training and employment to populations at risk of chronic unemployment such as NEET youth. The enterprise has had previous experience in apprenticeship training over the last 5 years, with 42 apprentices enrolled in their vocational training programs. The city of Barrie is located in Central Ontario with a population of approximately 147 000 (<https://www.city-data.com/canada/Barrie-City.html>). Approximately 20% of the population is between the ages of 15 to 30 years. The unemployment rate is 6.0%. 93% of residents speak English only, with 1% French only. Only 6.7% of citizens are visible minorities, and 2.1% identify as Indigenous. Prevalence of low income after taxes is 11.6%. Barrie is one of Canada’s fastest growing communities, with a growth rate exceeding 4.5% over the previous 5 years. The city of Sudbury is located in Northern Ontario with a population of approximately 85 000 (<https://www.phsd.ca/resources/research-statistics/health-statistics/2016-demographic-profile-public-health-sudbury-districts/>). Approximately 13% of the population is between the ages of 15 to 30 years. The unemployment rate is 8.5%. 70% of residents speak English only, with 24.7% French only. Only 1.2% of citizens are visible minorities, and 17.5% identify as Indigenous. Prevalence of low income after taxes is 11.6%. The population growth rate was less than 1% over the last 5 years. In each city, the TDTP will consist of both in-class and on-site learning opportunities as previously described.

# 10 Eligibility

Participants must provide written, informed consent before any study procedures occur.

## 10.1 Inclusion criteria

Participants eligible for the trial must comply with all of the following at randomization:

1. Enrolled in one of the TDTP cohorts

2. Must have an active Ontario Health Insurance Plan number

3. Must have a valid Canadian Social Insurance Number

4. Access to Wi-Fi network

5. Must be between the ages of 18 to 49 years of age

## 10.2 Exclusion criteria

1. Language barrier (non-English or French) compromises the participant’s ability to complete the self-report tool for distress

# 11 Interventions

## 11.1 Distress thermometer

This study will use the Distress Thermometer screening tool to create a self-reporting, web-based application to monitor distress in apprentices that may lead to absenteeism, drop-out or unemployment (17,18). The Distress Thermometer is a validated tool for identifying and measuring the severity of psychological distress. While originally validated in cancer patients, it has been used in many other clinical and non-clinical populations (19). The Distress Thermometer is a single-item visual analog scale from 0 (no distress) to 10 (extreme distress). The patient is asked to rate their level of distress over the previous week using this scale. The threshold for concerning levels of distress varies depending on the clinical context, but has been found to range between 3 and 5 in cancer patients, with the median cut-off of 4 maximising the sensitivity (median 0.83, range 0.5 to 1.0) and specificity (median 0.68, range 0.36 to 0.98) (18). After rating their distress, the patient is asked to identify one or many causes from a pre-established list of 39 potential items that commonly result in distress. These 39 items are categorized into 5 domains: practical problems; family problems; emotional problems; spiritual/religious concerns; physical problems. The tool has been translated into 21 languages, and 18 have validated the tool, including French (20). The biggest advantage of the Distress Thermometer compared to other tools is its ease of administration and interpretation, and brevity of use. Once screening with the Distress Thermometer is completed, the next decision is whether or not the user needs to be referred for psychosocial support. A barrier to using the Distress Thermometer is the ambiguity of the meaning of distress. In this study, a definition of distress will be provided to the user to minimize confusion. This definition is derived from the National Comprehensive Care Network Distress Management Panel, and will be modified to the following; “an unpleasant experience with a psychological, social, financial and/or physical nature that may interfere with your ability to cope effectively with the stressor” (19). Another barrier is the extensive list of potential sources that may not be relevant in non-oncologic users. We will reduce the number to 9 from the original 39 to those that are most relevant in this population. Another barrier is the variation associated between the distress rating and the need for referrals for help. In response, we will include an additional question after the user has completed the VAS and identified the potential cause(s) contributing to distress that asks, “Will your distress stop you or will your distress cause you to do something that would stop you from showing up for class or work today?”. This last question is intended to be used in conjunction with the distress rating to identify those users most at risk for absenteeism or drop-out.

## 11.12 Web-based, self-report tool for distress

The Distress Thermometer screening tool will be integrated into a web-based, self-reporting tool that apprentices will be asked to complete on a daily basis (Monday to Thursday) prior to attending their in-class or on-site session for the 12-week duration of the TDTP. Apprentices whose cohorts are randomized to either ICM^10^ or ICM^11^ will be provided with a tablet computer to access the Distress Thermometer screening tool. Apprentices will login using a unique username and password system. The Case Manager will have immediate access to each apprentice’s daily distress score, including all of their previous scores. The scores will be prioritized according to the following criteria:

1. High Priority Distress score ≥ 4 + Answer “Yes” to last question, or

Answer “Yes” to last question

A referral may also be made if the apprentice’s distress level is escalating defined as a change of ≥ 2 on the distress score from previous day.

2. Medium Priority Distress score≥4 + Answer “No” to last question

3. Low Priority Distress score ≤3 + Answer “No” to last question

The Case Manager will immediately contact (by phone) all apprentices in the high priority group to coordinate a care management plan personalized for their identified stressor(s). For those apprentices identified as medium priority, a one-on-one in-person meeting with the Case Manager will be scheduled to occur within 48 business hours in order to coordinate a personalized care management plan for their identified stressor(s). For those apprentices identified as low priority, a quick check-in with the Case Manager will take place within the work week to determine if any special care management issues need to be addressed. The care management plan is not dictated by the study but is left to the discretion of the Case Manager and apprentice. The care management plan will be documented within the web-based, self-report tool.

For those apprentices who do not compete a daily assessment by 8 am, the Case Manager will reach out by email/phone immediately to the apprentice to enquire about their status. For those apprentices experiencing severe distress, they have the option of directly contacting (email/phone) the Case Manager instead of completing the Distress Thermometer screening tool.

## 11.2 Mental health & addictions

When an apprentice has been identified as being in a high priority group due to a mental health or addictions stressor, the Case Manager will contact (by email or text message) the triage counsellor for the MH&A program intervention. After this initial contact, a standard referral form will be sent to the Case Manager at Community Builders to complete and return to the MH&A triage counsellor. The triage counsellor will review the referral form immediately and schedule an appointment with a MH&A healthcare provider. The timing of the appointment will be determined by the triage counsellor but will always occur within 24 to 48 hours of the referral. The triage counsellor will also determine the need for an in-person versus audio/video consultation.

For any apprentice identified as being at high risk for suicide, the triage counsellor will instruct the Case Manager to take the apprentice to the RVRHC Emergency Department where they will be assessed by the MH&A crisis team.

For any apprentice identified as being in either drug withdrawal or relapse, the triage counsellor will schedule an appointment with healthcare providers at the RVRHC Rapid Access Addiction Medical clinic. The appointment will always occur within 24 to 48 hours of the referral.

For any apprentice that requires treatment or admission to a MH&A program that limits their availability to complete the TDTP, they will be withdrawn from their cohort and enrolled in a subsequent TDTP cohort after resolution of their health-related issues. For all other apprentices who access MH&A services, they will continue to attend their TDTP and continue to be supported according to their allocated case management model.

